### Exploratory Analyses {27d}

As an exploratory analyses, mediation models will be used to examine if factors within the Intergenerational Transmission of Stress Model (e.g., parenting quality, parenting stress, family and system level factors) are potential mediators of both parent and child well-being.

### Definition of analysis population related to protocol non-adherence and methods to handle missing data {27c}

The LightBEAM program will employ an intent-to-treat analysis using maximum likelihood estimation, whereby all participants, regardless of study completion and adherence, will be included in analysis based on their initial randomization. To account for treatment adherence, de-identified analyses will be conducted using only data from participants who completed the LightBEAM intervention.

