### Trial design {12}

Using a two-arm clinical design, participants will be randomized in a 1:1 allocation to be placed in either the 12-week LightBEAM program or the waitlist control. After the 12-week LightBEAM program has been completed by the intervention condition, participants in the waitlist control group will have one month to complete the “re-baselining questionnaires and online orientation prior to gaining access to the LightBEAM intervention. Participants in the intervention condition will complete post-questionnaires at the same time that the waitlist control completes re-baselining questionnaires. Longitudinal self-report questionnaires will be administered digitally at three timepoints: pre-intervention, post-intervention, and at six months follow-up.

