11	Boundary setting to make space for everything else	Memory making with your kiddo
12	Staying well and moving forward	Recipe for wellness

#### Aim 2

All eligible participants must present with at least one elevated symptom of concern across parental anxiety (GAD-7), depression (PHQ-9), anger (PROMIS) and/or parenting stress (PSI). Based on which metric(s) participants screen in as being elevated, an individualized composite primary score will be created whereby we examine whether there is a statistically significant change in elevated symptoms of concern across assessment time points. To examine the efficacy of the LightBEAM program in improving parental outcomes, a multi-level model with random intercepts will be utilized to assess the effect of treatment over time based on conditions. An intent to treat approach will be followed such that all randomized participants are included in analysis, regardless of completion.

Specifically, we will examine pre-to-post-to follow up program changes in primary and secondary outcomes. Such analysis will allow us to examine the efficacy of the LightBEAM program compared to other community resources. Program engagement metrics (e.g., number of videos watched, see Table 4) will also be included as moderators to probe whether participant changes are due to program engagement. This dosage analysis will be an exploratory analysis.

**Table 4 Tab4:** Aim 1 feasibility and acceptability metrics

	Indicator	Benchmark	Rational
Recruitment Rate	Number of parents recruited per month	Approx. 50 parents	We want at least 50 parents in the forum to ensure maximum engagement
Retention Rate	% of parents with follow up data	> 70% of parents with follow up data	Average retention rate amongst previous MOOI’s is 70%
Forum Use	# of posts and comments made on the forum	> 50% of users engage at least once in the forum (i.e., through posting, responding or interacting with a message)	This is an exploratory outcome. Based on previous work that showed 57% engagement in the BEAM forum
Videos watched	% of videos watched at least 50% of the way through	Participation in > 50% of the LightBEAM Content	Utilizing same benchmark (e.g., 50%) used in previous BEAM pilot studies [13]
Symptom tracking	# of weekly surveys completed	Participation in > 50% of symptom tracking exercises	Based on benchmark used in previous BEAM pilot studies

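### The supporting adherence analyses (completers only, and engagement as a moderator) condition on events that, up to post-intervention, can occur only in the LightBEAM arm, so they cannot isolate a programme effect; the intention-to-treat result is unaffected

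*Protocol article*

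**What the plan says.** The section on the analysis population {27c} sets intention to treat as the main approach: "all participants, regardless of study completion and adherence, will be included in analysis based on their initial randomization". The next sentence adds that, as an account of adherence, "de-identified analyses will be conducted using only data from participants who completed the LightBEAM intervention". It does not define completion there, name a comparator, or label the analysis exploratory or supportive.

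Under Statistical methods {27a, b}, Aim 2, engagement metrics such as the number of videos watched "will also be included as moderators to probe whether participant changes are due to program engagement". The article then qualifies this: "This dosage analysis will be an exploratory analysis". The time frame of the Aim 2 model is given as "we will examine pre-to-post-to follow up program changes in primary and secondary outcomes".

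The design section {12} says participants are "randomized in a 1:1 allocation to be placed in either the 12-week LightBEAM program or the waitlist control". Controls complete re-baselining questionnaires and the "online orientation prior to gaining access to the LightBEAM intervention". The sections on re-baselining and on the orientation session confirm this order. The randomised contrast between access and no access therefore ends when the waitlist is admitted.

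**The concern.** Completion and engagement are both determined after randomisation. Until the post-intervention assessment they are possible in one arm only. Restricting to completers, or splitting by engagement, therefore selects on one side of the comparison by a characteristic that may be related to prognosis. Parents who are improving anyway, or who are better organised or supported, may be more likely to keep using an app.

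At stake is how a null or weak result is reported. An ineffective programme could show an apparent benefit among those who completed it, together with a convincing dose-response gradient. The first would be offered as an account of adherence and the second as evidence that engagement produced the change.

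**Working it through.** The article gives no figure to reproduce: no completion rate, effect size, SD or power. The steps below set the passages against each other and then size the bias under stated assumptions, always with zero programme effect.

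**1. Who can be a completer before the waitlist is admitted?** Only LightBEAM participants. The completers sentence then has two readings.
- Literal: only completers are analysed. No concurrent control remains, and what is left is pre-post change in one arm.
- Generous: completers are compared with all waitlist participants. A self-selected subset is set against an unselected arm.

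**2. Generous reading: selection bias.** Let p be the share of LightBEAM participants who complete, and g the prognostic difference (in SD) between completers and non-completers. Randomisation makes the waitlist mean equal to p × (completers' mean) + (1 − p) × (non-completers' mean). Completers minus waitlist is therefore (1 − p) × g.

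| p (assumed) | g = 0.2 | g = 0.5 |
|---|---|---|
| 50% | 0.5 × 0.2 = 0.10 | 0.5 × 0.5 = 0.25 |
| 70% | 0.3 × 0.2 = 0.06 | 0.3 × 0.5 = 0.15 |

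The range is 0.06 to 0.25 SD.

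**3. Simulation check.** Settings: 1:1 allocation, N = 200 or 500 (the ends of the planned range), 1,500 replicates per cell, two-sided 5% (assumed). Engagement has correlation r with the improvement that would occur anyway, and completers are the top 50% on engagement.
- Bias by formula is r × φ(0)/0.5. For r = 0.3 this is 0.3 × 0.399/0.5 = 0.24 SD, which corresponds to g = 0.24/0.5 = 0.48.
- At r = 0.3 the completers contrast is significant in 30% (N = 200) and 61% (N = 500) of trials with full retention, and in 23% and 45% with 70% retention.
- The within-arm engagement gradient at r = 0.3 is significant in 70 to 88% (N = 200) and 98 to 99.9% (N = 500) of trials, over completion shares of 30 to 70% and both retention levels. The association is real, but by construction the programme did not cause it.
- The as-randomised comparison stays near 5% in every cell (0.035 to 0.063).
- At r = 0 all tests stay near 5%. The bias depends entirely on engagement being prognostic.

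**4. Literal reading: regression to the mean.** Participants are selected on the screener, but Table 1 repeats the PHQ-9, GAD-7, PROMIS Anger and PSI at pre-intervention, and Aim 2 starts from pre. Assume selection above +0.5 SD on one scale. The mean excess at screening is φ(0.5)/(1 − Φ(0.5)) = 1.141 SD.
- Equal correlations across occasions: all the regression occurs between screener and pre, so pre-to-post regression is zero.
- Correlation decaying as AR(1) with parameter ρ: the excess is ρ × 1.141 at pre and ρ² × 1.141 at post, a fall of ρ(1 − ρ) × 1.141. For ρ = 0.6, 0.7 and 0.8 this is 0.27, 0.24 and 0.18 SD.

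Natural recovery comes on top and cannot be separated from a programme effect without a control.

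**5. Engagement moderator.** Before the waitlist is admitted, videos watched is zero or undefined in every control. The modification of the randomised effect by engagement cannot then be estimated from the data. What can be estimated is the association of engagement with change inside the LightBEAM arm, which step 3 shows can be strong with no programme effect.

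**The case against.** The strongest reply is that these are supporting analyses. Intention to treat is stated directly before the completers sentence and again under Aim 2, and the dosage analysis is expressly exploratory. The article does not say that the engagement model spans both arms, and details of comparator and model may sit in a fuller plan. All of that stands, and it limits the point to interpretation of supporting results. It does not answer the point: the text fixes the completers-only restriction without such a label, and the exploratory label on the dosage analysis does not make its stated causal purpose attainable.

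Several stronger readings are tempting, but the documents do not support them.
- A reader might infer that the main efficacy estimate is compromised. It is not.
- A reader might infer that both analyses are offered as proof of cause. Only the engagement sentence uses causal wording; the completers sentence speaks of accounting for adherence.
- A reader might infer that completion and engagement never exist in the waitlist. They can after it is admitted, but there is then no concurrent untreated control, so this rescues neither analysis.
- A reader might apply the full screener-to-next-measurement regression, (1 − ρ) × 1.141 = 0.23 to 0.46 SD for ρ from 0.8 to 0.6. That ignores the separate pre-intervention measure. Co-parents, moreover, are not selected on distress.
- A reader might take the 50% benchmark in Table 4 as an expected completion rate. It is a share of content, not of participants.

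**Conclusion.** The point holds for the supporting adherence analyses. As written, the completers-only analysis either drops the concurrent control or breaks the randomised comparison, and the engagement analysis cannot show what it is meant to probe.

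Under the assumptions shown, an ineffective programme could appear to help completers by 0.06 to 0.25 SD against all controls. On the literal reading, regression to the mean adds between zero and about 0.18 to 0.27 SD pre to post, depending on the correlation structure, plus natural recovery. The direction of the bias assumes that those who engage have the better prognosis; with no such link the selection bias vanishes, but nothing in the plan ensures that. The structural argument does not depend on these figures.

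**What to change.** 1. State that intention to treat is the sole basis for efficacy claims.
2. Replace the completers-only analysis in {27c} with a complier-average causal effect that uses randomisation as the instrument, limited to pre-to-post, before the waitlist gains access. With no control access in that period, non-compliance is one-sided, which suits the method, and Mplus is already named.
3. Define compliance as any programme use, where the assumption that allocation affects outcome only through use is most plausible. Use the Table 4 benchmark of more than 50% of content as a sensitivity analysis, and state that it assumes no effect below that threshold; someone who watches fewer videos but tracks symptoms and uses the forum may still benefit.
4. Run the Aim 2 engagement analysis within the LightBEAM arm only, label it a non-causal association, and delete the clause that attributes change to engagement.

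The cost is a few sentences, a little more analysis work and wider intervals. In its simplest form the complier effect is the intention-to-treat difference divided by the compliant share, so its interval widens by roughly 1/0.7 = 1.4 times at 70% compliance and 1/0.5 = 2 times at 50%. When the intention-to-treat effect is zero, the complier estimate is zero as well, a property the completers analysis lacks.

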## Methods: monitoring

### Composition of the data monitoring committee {28a}

Given the minimal risk associated with this trial design, recruitment, randomization, and data collection procedures will be monitored by the Principal Investigator and study coordinators. A formal data monitoring committee will not be implemented. Additionally, a Canada-wide team of Co-Investigators will be consulted throughout the study design, implementation and data analysis procedures.

### Interim analysis {28b}

After the first 100 participants have completed the LightBEAM program, an interim data analysis will occur. Specifically, graduate students, principal investigators and senior research assistants will conduct preliminary analysis to assess how LightBEAM has succeeded in addressing the three proposed aims. This initial analysis will help the team identify if the translation of BEAM to LightBEAM is effective at supporting parental mental health and parenting. This will allow the team to re-evaluate the study design and implementation if results suggest we are not adequately achieving such effectiveness. De-identified analyses will be shared with larger co-investigators to assess efficacy of LightBEAM.

### Frequency and plans for auditing trial conduct {29}

Our research team has no plans to conduct an internal audit during this trial. The Research Ethics Board at the University of Manitoba may conduct an external audit of this research project.

## Ethics and dissemination

### Research ethics approval {30}

This protocol was approved by the University of Manitoba Research Ethics Board August 2024 [HE2024-0152]. All adverse events will be reported to the University of Manitoba Research Ethics Board, in accordance with their protocols and policies.

### Protocol amendments {31}

All required protocol amendments will be submitted and implemented in accordance with the University of Manitoba’s REB protocols.

### Confidentiality {33}

All efforts will be made to protect participant confidentiality throughout the course of the LightBEAM program in accordance with the University of Manitoba's Research Ethics Board policies. Participant data and identifying information will be stored separately within a password protected SharePoint account maintained by the University of Manitoba. Furthermore, all research personnel will be TCPS and PHIA certified and complete an oath of confidentiality. Additionally, efforts will be made to protect confidentiality during the online orientation sessions and within the group forum. Participants will be informed that confidentiality may be breached in the event that imminent danger to self or others is disclosed to researchers, including child maltreatment or in the event of a court subpoena.

### Access to data {6}

All data will be stored in a secure location accessible by study coordinators and Principal Investigators. Participant level data will not be made available. Summary statistics, statistical code, and questionnaire data will be made available upon reasonable request.

### Ancillary and post-trial care {34}

All participants will receive a list of crisis resources upon completion of the eligibility screener. A provincial-specific list of community resources and counselling services will be provided to participants via email if they are not eligible to participate in the LightBEAM study.

### Dissemination and policy {8,11}

Efforts will be made to disseminate findings broadly to both academic and public audiences through implementation of an integrated knowledge mobilization plan. Specifically, a series of knowledge mobilization presentations geared towards both lay and academic audiences will be used to disseminate findings in tangent with academic articles published in peer review and open access journals. All participants will be asked during the informed consent process if they would like a copy of the results. Additionally, findings will be shared with collaborating agencies, community partners and policy makers through various community facing presentations.

## Discussion

The LightBEAM program is a light touch extension of our previous program BEAM, which evidenced improvement in mental health and parenting outcomes across several large-scale randomized trials (see Joyce et al. [13], MacKinnon et al. [21]). The LightBEAM program has the potential to offer Canadian families evidenced-based mental health support by translating a previously established intervention into an easily accessible app based MOOI. By creating a program that is free, user-friendly, and widely accessible across Canada, we negate common barriers faced by Canadian families when accessing mental health resources (i.e., long wait times, limited services in rural communities), thereby mitigating the negative downstream impact of untreated parental mental health concerns on child and family development. Findings will provide information on the feasibility, acceptability, and efficacy of the LightBEAM program. Results and participant feedback will be used to inform and improve future iterations of the LightBEAM program. Pending evidence for both the feasibility and acceptability of the LightBEAM program, future aims include the potential for adaptations tailored to fit different cultural, community, and/or diagnostic contexts.

### Trial status

This trial has been registered on ClinicalTrails.gov NCT07026838. Recruitment is set to begin in March 2025. We anticipate that the first 100 participants will be enrolled throughout the spring of 2025, with their 12-week program finishing in July of 2025. Recruitment is anticipated to end by December 2025.

## Data Availability

No datasets were generated or analysed during the current study.

## Appendix 1

### Sample LightBEAM focus group questions

1. Can you tell me about your experience accessing the LightBEAM eHealth mental health service? What was your experience with this service?
2. Can you tell me how relevant you felt the parenting content you saw on LightBEAM was? Was the content helpful to you as a parent?
3. Can you tell me how relevant you felt the mental health content you saw on LightBEAM was? Was the content helpful to you as a parent?
4. What were your favorite and least favorite components of LightBEAM
5. What made the program easy to use?
6. Where there any barriers to accessing this service?
7. Were any aspects of the program hard to use? Did any of the program components feel irrelevant?
8. What else would you like to see in the LightBEAM Program?
9. Would you recommend this program to a friend?

## Appendix 2

### LightBEAM acceptability metric

*Response options range from Agree to Disagree on a seven-point Likert scale.*

1. The App was very easy to use
2. It was easy for me to learn to use the app
3. The navigation was consistent when moving between the screens
4. The interface of the app allowed me to use all the functions (such as entering information, responding to reminders, viewing information offered by the app)
5. Whenever I made a mistake using the app, I could recover easily and quickly
6. I like the interface of the app
7. The information in the app was well organized so I could easily find the information needed
8. The app adequately acknowledged and provided information to let me know the progress of my action
9. I feel comfortable using the app in social settings
10. The amount of time involved in using the app has been fitting for me
11. I would use this app again
12. Overall, I am satisfied with this app
13. The app would be useful for my health and well-being
14. The app improved my access to healthcare services
15. The app helped me manage my health effectively
16. This app has all function and capabilities I expected it to have
